## Abstract

**Introduction:**

Diabetes in pregnancy presents a unique physiological challenge to manage glycaemia while maintaining adequate nourishment for the growing fetus. Women with diabetes who become pregnant are at greater risk of adverse maternal and newborn outcomes, compared with women without diabetes. Evidence suggests that control of (postprandial) glycaemia is key to manage maternal and offspring health but it is not yet clear (1) how diet and lifestyle moderate these shifts across the full duration of pregnancy or (2) what aspects of maternal and offspring health are associated with dysglycaemia.

**Methods and analysis:**

To investigate these gaps, a cross-over randomised clinical trial has been embedded within routine clinical care. Seventy-six pregnant women in their first trimester with type 1 or type 2 diabetes (with or without medication) attending their routine antenatal appointments at National Health Service (NHS) Leeds Teaching Hospitals will be recruited. Following informed consent, data on women’s health, glycaemia, pregnancy and delivery will be shared by the NHS with researchers. At each visit in the first (10–12 weeks), second (18–20 weeks) and third (28–34 weeks) trimester, participants will be asked for consent to: (1) lifestyle and diet questionnaires, (2) blood for research purposes and (3) analysis of urine collected at clinical visits. Additionally, participants will be asked to consume two blinded meals in duplicate in second and third trimester. Glycaemia will be assessed by continuous glucose monitoring as part of routine care. The primary outcome is the effect of experimental meals (high vs low protein) on postprandial glycaemia. Secondary outcomes include (1) the association between dysglycaemia and maternal and newborn health, and (2) the association between maternal metabolic profiles in early pregnancy with dysglycaemia in later pregnancy.

**Ethics and dissemination:**

The Leeds East Research Ethics Committee and NHS (REC: 21/NE/0196) approved the study. Results will be published in peer-reviewed journals and disseminated to participants and the wider public.

**Trial registration number:**

ISRCTN57579163.

STRENGTHS AND LIMITATIONS OF THIS STUDYThe analyses of response to meals alongside repeated measures of blood and urine metabolite profiles will offer insight into distinct shifts in metabolism during pregnancy in women with type 1 and type 2 diabetes, and their association with maternal and newborn health in pregnancy and at delivery.The trial is embedded within standard clinical care and uses routine data and biological samples collected by health services to minimise (1) participant burden and (2) non-essential participant contact, which reduces risk of bias and will permit the study to continue even with the re-introduction of public restrictions.As with all observational data, participant recall data (sleep, physical activity and diet) are subject to social desirability bias but the inclusion of repeated and complementary measures (ie, metabolite) will allow this to be evaluated in future analysis.INFORMED is being conducted with the National Health Service of the UK; therefore, its results may not be directly generalisable to other nations or government health services.

## Introduction

### Background and scope

Pregnancy naturally induces a state of mild insulin resistance (IR) to shuttle more nutrients to the growing baby; however, in women with diabetes in pregnancy (DIP), excessive IR and persistent hyperglycaemia increases the risk of adverse pregnancy outcomes.^1–4^ Globally, the prevalence of DIP is on the rise, affecting ~17% of all pregnancies.^4 5^ Compared with women without diabetes, women with DIP are at elevated risk of pre-eclampsia, preterm delivery and mortality, while their offspring are at increased risk of unhealthy weight (<2.5 kg or >4.5 kg), dysglycaemia, injuries at birth, and higher risk of type 2 diabetes mellitus (T2DM) and cardiovascular disease in later life.^1 5 6^

Postprandial glycaemic control is important for healthy pregnancy outcomes.^1 6^ Evidence supports a healthy diet and lifestyle—that includes whole grains, fruits and vegetables, and regular physical activity—as the cornerstone for managing DIP, which is effective in 70%–85% of women with DIP.^7–9^ National Institute for Health Care Excellence (NICE) UK guidelines primarily focus on improving carbohydrate quality by including more low glycaemic index (GI) foods as part of a balanced diet including whole grains, fruits and vegetables to manage glycaemia during pregnancy.^7^ Although low GI diets do support the management of mean glucose levels, their effect on reducing episodes of hypoglycaemia and hyperglycaemia and ability to reduce maternal and offspring risk of complications is not clearly established.^10^ Alternatively, emerging evidence in preclinical and human studies suggests that the amount of maternal protein intake can improve management of dysglycaemia in DIP,^11^ but its effect on metabolism and 24-hour dysglycaemia in pregnancy is unknown. Finally, some women find it challenging to consistently follow a balanced diet, due to barriers such as availability, accessibility and affordability of healthy foods, lack of time and cooking skills^7 9^ therefore, a cost-effective nutritious meal replacement may be useful for supporting healthy eating habits. Most recently, we noted that ‘morning’ is when pregnant women with diabetes struggle most to manage glucose levels within a healthy range,^10^ suggesting that breakfast may be a particularly important point in the day to offer support for managing dysglycaemia.

Continuous glucose monitors (CGMs) are becoming routinely used in the UK National Health Service (NHS) in perinatal clinical settings for women with DIP.^1^ The unobtrusive patches record an individual’s glucose every 5 min for up to 14 days and offer quantitative information to identify interstitial glucose deviations over a 24-hour period. By measuring glucose continuously over hours and days, a more complete representation of dysglycaemia can be modelled and offer novel insight regarding the parameters that drive and associate with dysglycemia, and their impact on maternal and offspring health.^11^

Previous studies^12 13^ have uncovered new associations and identified novel points of interest for managing dysglycaemia during pregnancy and mediating health risks. However, our ability to inform new strategies to manage these new areas of concern are limited by our understanding of the contribution of biological, lifestyle, and environment exposures on dysglycaemia in early, mid, and late pregnancy and their moderating effect on maternal and offspring health. To address this gap in current understanding, this study aims to investigate the effect of breakfast meal replacements and dietary protein on glucose variability in pregnancy in women with pre-existing type 1 or type 2 diabetes.

### Aim and objectives

Our overall aim is to investigate postprandial CGM profiles throughout the course of the pregnancy and how they are associated with personal (lifestyle) characteristics and physiological parameters. Our primary research objective is to assess the effect of easy-to-prepare meals and dietary protein on dysglycaemia over the course of pregnancy. Secondary research objectives include (1) the association between dysglycaemia and maternal and newborn health, and (2) the association between maternal metabolic profiles in early pregnancy with dysglycaemia in later pregnancy.

## Methodology and analysis

### Participants

Women with type 1 diabetes mellitus (T1DM) and T2DM during pregnancy in their first trimester will be recruited from the DIP antenatal clinics at Leeds Teaching Hospitals NHS Trust (LTHT). Women will be approached by their direct clinical care team and given a study information flyer and invited to contact the research team (via phone or email) if they are interested to participate or if they wish to discuss the study in more detail. Women expressing interest at the end of the initial meeting will be emailed a participant information sheet and a web link to secure electronic informed consent. Once a secure electronic signature is provided, the participant’s eligibility will be assessed according to study inclusion and exclusion criteria.

### Sample size using power calculation

CGM data provide numerous metrics to offer unique insight into variations and deviations of glucose levels over time—area under the curve (AUC), mean glucose, coefficient of variation of glucose, mean amplitude of glucose excursions (MAGE) and time in range (TIR).^14^ Additionally, there is no current evidence regarding the effect of diet composition and glycaemic load on metrics of CGM in pregnant women with diabetes throughout the duration of pregnancy. Therefore, we have elected to focus on AUC as the primary metric because it is easily interpretable and commonly used to quantify postprandial glycaemia. Evidence from Fabricatore e*t al*^15^ demonstrated a significant association (p<0.05) between self-reported GI and measures of CGM (including AUC, mean glucose and % time hyperglycaemic) in a clinical trial of 21 women and 5 men with type 2 diabetes. Assuming similar effect sizes between GI (per unit) and AUC glucose (β=0.36 mg/dL/min; R^2^=0.38), mean glucose (β=0.02 mol/L; R^2^=0.38) and time spent >10 mol/L blood glucose (β=0.41%; R^2^=0.36), we will have sufficient power (power=0.90) to detect a significant pairwise effect of GI on these parameters with 63 participants. Another study by Law *et al* suggested that this will provide sufficient power (power=0.90) to compare subgroups of participants (stratified by body mass index (BMI), age, type of diabetes) and test for significant differences (of a minimum effect size) in AUC glucose (±61 mmol/L/min), mean glucose (±0.5 mmol/L) and % time hyperglycaemic (±3.7%).^16^ Finally, given the comparable proportions of women reported to be of white European versus non-white European ancestry (57% vs 43%) or diet versus diet+medication (46% vs 54%), we also anticipate having adequate power to compare these confounders of glycaemic response. To account for attrition, we will increase our recruitment target by 20% above our calculated, suggesting a target sample size of 76 recruited women. We have allocated ~6 months to recruit 76 women (at 10–12 weeks’ gestation) and ~15 months for study completion (ie, final delivery). All power analyses were performed using G*Power (V.3.1).^17^

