### Nested cross-over dietary meal intervention within the study

Shortly after their clinical visit at ~18–20 weeks and ~28–34 weeks, participants will be asked to consume standardised breakfast meal replacements in their own home, at breakfast time for 4 days. These will be two different experimental meals (A and B; matched for 400 kcal and 13 g of fat) consumed under free-living conditions. The experimental meals will appear and taste similar but differ in protein quantity which will alter how quickly the glucose in each meal is absorbed into the blood.^22^ One experimental meal will have 20 g of vegan and gluten-free protein powder added, which slows gastric emptying and glucose absorption into the blood to a rate that is comparable with commonly consumed whole-grain breakfast cereals (eg, steel-cut or rolled oats; GI ≈40). The other experimental meal will have no added protein. The experimental meals (labelled A or B) with a drink shaker are stored in a box by the research team in a COVID-19-safe laboratory. Each participant will be assigned to one of six random orders to consume the experimental breakfast meals (AABB, ABAB, BBAA, BABA, ABBA, BAAB) over 4 days using an online randomiser (https://www.random.org/integer-sets/). This will be done by block randomisation to assign 12–13 participants to each of the six possible orders of meal consumption, which the participant will follow for both sets of meals (i.e., ~18–20 and ~28–34 weeks). The participant will only need to pour the powder into the shaker, add cold water to the line marked on the cup (500 mL), and consume within 5 min.

The powder is a nutritionally complete meal replacement in drink form; every meal contains a balance of protein, carbohydrates, essential fats, fibre, plus all 26 essential vitamins and minerals, and phytonutrients. Additionally, the product is low in sugar, lactose-free, contains no nuts or palm oil, and has a long shelf life. The powder is commercially available and is produced in facilities that meet highest quality standards. This product was chosen to minimise time burden for participants and it is free from many commonly avoided food items (i.e., lactose, nuts, gluten and meat).

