### Statistical analysis considerations

All standard CGM metrics will be calculated, with AUC glucose as the primary CGM metric (mean±SD). The primary analysis will be the effect of dietary protein on AUC glucose for the 24-hour window immediately after each study meal. The analysis will be constructed as pairwise linear model with study meal (0=low protein, 1=high protein) regressed against 24-hour mean AUC glucose and adjusted for study parameters (e.g., randomised meal order) and participant covariates (e.g., maternal age, ethnicity, parity, BMI, gestational age, physical activity and sleep quality). Statistical significance will be set at p<0.05, where a p<0.05 for study meal will suggest a significant effect of dietary protein on 24-hour postprandial AUC glucose. The direction and significance of covariates will be investigated to identify study and participant mediators of the association. Statistical analysis will be conducted in R studio and SPSS (Ver. 29+).

Secondary research objectives include (1) the association between dysglycaemia and maternal and newborn health, and (2) the association between maternal diet in early pregnancy with dysglycaemia during pregnancy. These analyses will also be performed using regression models adjusted for covariates, with the assessment of early diet on longitudinal changes in dysglycaemia also adjusted for time points of AUC (i.e., mixed-model). The association between early maternal diet and AUC will be performed using three distinct dietary metrics (calculated from myFood24):

1. Overall diet quality

The association between diet quality and dysglycaemia will be assessed using an overall diet quality score.^24^ This scoring method has been modified and used previously to assess maternal diet quality in a multiethnic prospective birth cohort.^25^ The modified Alternative Healthy Eating Index (mAHEI) score is calculated using the following method; an individual will receive 10 points for each of the following food categories when they consume above or below a threshold of: ≥5 servings of vegetables, ≥4 servings of fruits, ≥1 serving of nuts or soy proteins, ≥3 servings of whole grains, a ratio of ≥4 servings of fish to 1 serving of meat and eggs, and ≤0.5 servings of less-healthy foods (i.e., fried foods and processed meats). Intermediate intake is scored proportionally between 0 and 10. The maximum mAHEI score is 60; the higher the score, the more healthful the participant’s diet.

2. Macronutrient

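### The 63 participants at 90% power cannot be reproduced from the stated GI association, and that association is not the primary high- versus low-protein contrast

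*Protocol article*

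**What the plan says.** In the protocol article, the section on sample size chooses AUC as the primary CGM metric. It then relies on a trial of 21 women and 5 men with type 2 diabetes in which self-reported GI was associated with CGM measures. The assumption is worded "Assuming similar effect sizes between GI (per unit) and AUC glucose (β=0.36 mg/dL/min; R^2^=0.38". The same R² is given for mean glucose, and 0.36 for time above the hyperglycaemia threshold. The conclusion is that "we will have sufficient power (power=0.90) to detect a significant pairwise effect of GI on these parameters with 63 participants". G*Power is named as the software, but not the test chosen in it. For attrition, "we will increase our recruitment target by 20% above our calculated, suggesting a target sample size of 76 recruited women".

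The comparison to be made is described elsewhere. Under the nested cross-over intervention, each woman takes two meals, each in duplicate over four days, at two gestational time points. The meals differ in protein: "One experimental meal will have 20 g of vegan and gluten-free protein powder added". The statistical analysis section makes the meal effect on 24-hour AUC the primary analysis, with adjustment for meal order and participant covariates. It says "Statistical significance will be set at p<0.05" and adds "where a p<0.05 for study meal will suggest a significant effect of dietary protein on 24-hour postprandial AUC glucose".

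**The concern.** There are two separate difficulties.

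First, the section prints effect size, power, N and software, so a reader can try to recover the N. R² values of 0.36 to 0.38 are large effects in a regression power calculation, and 63 looks far too many for 90% power.

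Second, the effect that is powered is an association with dietary GI in another population. The trial estimates a randomised within-woman difference between two meals that differ in protein. The precision of that difference depends on the SD of the paired difference, and an R² for self-reported GI says nothing about it.

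At stake is the only power claim that could apply to the primary comparison. Without a detectable meal difference, a reader cannot tell what size of protein effect the trial was planned to find.

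**Working it through.** **Inputs.** Power 0.90, N = 63, R² = 0.38 (AUC, mean glucose) and 0.36 (time hyperglycaemic), from the sample size section. Alpha 0.05, from the statistical analysis section, which does not say one- or two-sided.

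**Step 1: try to reproduce 63.** Regression F test with f² = R²/(1 − R²), noncentrality f² × N and N − p − 1 denominator degrees of freedom for p predictors:

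- R² = 0.38: f² = 0.38/0.62 = 0.613
- R² = 0.36: f² = 0.36/0.64 = 0.5625

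Smallest N with power of at least 0.90:

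| Test | R² = 0.38 | R² = 0.36 |
|---|---|---|
| One predictor | 20 | 21 |
| One coefficient among 8 | 21 | 22 |
| One coefficient among 10 | 22 | 23 |
| Omnibus, 8 predictors | 40 | 43 |
| Omnibus, 10 predictors | 44 | 47 |
| Omnibus, 15 predictors | 53 | 56 |
| Omnibus, 20 predictors | 61 | 64 |

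As a correlation √R² (Fisher z, two-sided), N is 24 or 25. With one predictor and N = 63, power is above 99.99%. Run in reverse, 90% power at N = 63 with one predictor corresponds to R² = 0.147, which the article does not contain. Only the omnibus test with about 20 predictors comes close to 63. That number of predictors is not stated, and such a test would not isolate the effect of the meal.

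**Step 2: try to carry the slope over to the meals.** The AUC slope is 0.36 mg/dL/min per GI unit, so meal difference = 0.36 × GI gap. The article likens the protein meal to foods of GI about 40 and gives no GI for the other meal, so the gap is unknown. Purely as an illustration, assume a gap of 20: 0.36 × 20 = 7.2 mg/dL/min. Then assume an SD of the paired difference of 10, 20 or 30 mg/dL/min. The required N for 90% power (paired t-test, two-sided 5%) is 23, 84 or 185. The result rests entirely on two quantities that the article does not give.

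**Step 3: what 63 completers deliver for the primary contrast.** Paired t-test, two-sided 5%, noncentrality d × √n, where d is the mean high-minus-low difference divided by the SD of the per-woman difference. Solving for power 0.90 at n = 63 gives d = 0.415.

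| True d | Power with 63 | N for 90% |
|---|---|---|
| 0.2 | 35% | 265 |
| 0.3 | 65% | 119 |
| 0.4 | 88% | 68 |
| 0.5 | 97% | 44 |

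**Step 4: attrition.** 63 × 1.2 = 75.6, rounded to 76, which agrees with the wording. 1 − 63/76 = 17.1%, so 76 recruits leave 63 completers after about 17% loss. A 20% loss gives 76 × 0.8 = 60.8. With 60 or 61 completers, power at d = 0.415 is 0.885 or 0.890.

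**The case against.** The best defence is that an article condenses the full protocol. The G*Power test and number of predictors may be recorded there, and the planned model has open-ended covariate lists, so a figure of 20 participants is only one configuration. That stands, and it is why the finding is that 63 is not reproducible from what is stated, not that 20 is the right number. It does not rescue the paragraph, because the configuration that comes near 63 does not test the meal. The second mismatch, GI association against protein contrast, does not depend on the G*Power settings at all.

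It can also be said that protein is meant to act through slower glucose absorption, so GI is a reasonable proxy, and that the article calls the work a pilot and feasibility study and notes the lack of evidence in pregnancy. A proxy is acceptable if it is converted into a meal difference, but the GI gap needed for that is absent.

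Some stronger readings are tempting and not supported:

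- **That the trial is underpowered.** Nothing shows this. Duplicate meals at two time points may reduce the SD of the per-woman difference, and 63 women suffice if the true difference is about 0.415 SD or more.
- **That the authors entered 0.36 as a one-sided correlation.** That gives 63.3, hence 64, and other misreadings also land near 63 (0.38 as a one-sided standardised paired difference gives 61). The documents do not show which, if any, was used.
- **That the cited slope is between persons.** The article does not say so.
- **That 76 is miscalculated.** It matches the stated 20% increase.
- **That a null result would be uninterpretable.** A confidence interval for the meal difference would still be informative.

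**Conclusion.** The point holds as a fault in what is written. The stated 90% power at 63 participants does not follow from the stated R² values under a test of one predictor (20 to 23 needed) or an omnibus test of eight (40 to 43). Nor does it apply to the primary within-woman protein contrast, for which no target difference, paired SD or GI gap is given. The other power statement in the section concerns subgroups of participants, so it does not fill the gap.

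The regression figures assume alpha 0.05 in the F test. The detectable difference of 0.415 SD assumes a two-sided 5% paired t-test on one summary difference per woman; one-sided, it would be 0.373. Whether 0.415 SD is plausible or clinically relevant cannot be judged from the article. The fault lies in the justification, not in the design, the N or the analysis, so it should be corrected but does not threaten the trial.

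**What to change.** Replace the GI-regression justification with a power statement for the primary contrast, leaving N unchanged. For example: with 63 completers, a two-sided 5% paired t-test has 90% power for a mean high-minus-low-protein AUC difference of about 0.415 SD of the per-woman difference, and about 88%, 65% and 35% power at 0.4, 0.3 and 0.2 SD.

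Translate this into the AUC units used for analysis over a range of paired SDs labelled as an assumption. Assumed SDs of 10, 20 and 30 mg/dL/min, for instance, give detectable differences of 0.415 × 10 = 4.15, 0.415 × 20 = 8.3 and 0.415 × 30 = 12.45 mg/dL/min. Add that averaging duplicate meals and two time points may reduce the SD. If a sourced target difference and paired SD exist, cite them; that would be stronger than a detectable difference at fixed N.

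Optionally, note that 76 recruits leave 63 completers after about 17% loss, and that at 20% loss (60 to 61 completers) power at 0.415 SD is about 0.89.

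The cost is one rewritten paragraph, with no extra participants and no change to the conduct or analysis of the trial. The general assurance of 90% power becomes a conditional one.

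### Covariate main effects cannot identify mediators of the meal effect, and the 90% subgroup power is unsupported and does not extend to differences in meal response

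*Protocol article*

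**What the plan says.** The protocol article's section Sample size using power calculation makes three linked claims.

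- For the overall effect: "we will have sufficient power (power=0.90) to detect a significant pairwise effect of GI on these parameters with 63 participants". The inputs come from a study in type 2 diabetes, including "AUC glucose (β=0.36 mg/dL/min; R^2^=0.38").
- For subgroups, citing a second study: "this will provide sufficient power (power=0.90) to compare subgroups of participants (stratified by body mass index (BMI), age, type of diabetes"). The smallest differences that this is said to cover are listed as "AUC glucose (±61 mmol/L/min), mean glucose (±0.5 mmol/L) and % time hyperglycaemic (±3.7"%).
- For ancestry and medication: "we also anticipate having adequate power to compare these confounders of glycaemic response". The only basis offered is how the women divide on each factor, namely "white European versus non-white European ancestry (57% vs 43%) or diet versus diet+medication (46% vs 54"%).

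The section Statistical analysis considerations regresses 24-hour AUC glucose on study meal (low v high protein). It adjusts for meal order and for covariates such as maternal age, ethnicity, parity, BMI, gestational age, physical activity and sleep quality. No meal-by-covariate term is described. The same paragraph then states: "The direction and significance of covariates will be investigated to identify study and participant mediators of the association".

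The section Outcomes of interest mentions moderating effects of genetics, metabolism, diet and lifestyle in general terms, and labels all secondary analyses exploratory.

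**The concern.** The two sections together invite two misreadings of the results.

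First, a covariate that only predicts glucose level would be reported as explaining the protein effect. Higher BMI going with higher AUC, for example, would be called mediation of the meal effect, although nothing in the model examines how BMI and the meal act together. This rule sits in the primary-analysis paragraph. It is a stated rule of inference, not a detail left for later.

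Second, the sentence claiming 90% power for subgroups follows directly on the 90% claim for the overall effect and relies on the same 63 women. A reader may take it that the trial can also tell whether the protein effect differs by BMI, age or diabetes type, and so read a null subgroup result as good evidence of no difference. The protocol gives nothing to support that.

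**Working it through.** **1. What the covariate coefficient estimates.** Let M be the meal (0 low, 1 high protein) and X a covariate.

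- Model as described: AUC = μ + βM + γX + error. The meal effect at any X is (μ + β + γX) − (μ + γX) = β. It does not involve γ, so the sign and p-value of γ say nothing about the meal effect.
- Differential response needs AUC = μ + βM + γX + δ(M×X) + error. The meal effect is then β + δX, and the relevant term is δ, which the plan does not describe.
- Mediation needs the meal to change X, and X in turn to change AUC. The randomised meal cannot change age, ethnicity, parity or BMI.
- Every meal order contains two A and two B days, so with complete data a woman-level trait is balanced between the meals. Adding it to this linear model leaves the estimate of β unchanged.

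**2. The plan's own figures.** The subgroup power of 0.90 cannot be reproduced, because no SD is stated. The overall figure of 63 does not follow from the stated R² either. With R² = 0.38 and one tested predictor, f² = 0.38/0.62 = 0.613, and 90% power needs about 20 women (noncentral F, two-sided 0.05). With R² = 0.36 it needs about 21.

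**3. What the subgroup claim requires, read as a difference in glucose level.** Inputs: 63 women and the differences 61, 0.5 and 3.7 from the protocol. Assumptions: two-sided α = 0.05, and a near-equal split of 32 v 31. The noncentral two-sample t test gives 90% power at a standardised difference of d = 0.83. The largest admissible SD is the difference divided by d:

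| Metric | Difference | Largest SD, 32 v 31 | Largest SD, 42 v 21 (d = 0.88) |
|---|---|---|---|
| AUC | 61 | 61/0.83 ≈ 73 | 69 |
| Mean glucose, mmol/L | 0.5 | 0.5/0.83 ≈ 0.60 | 0.57 |
| % time hyperglycaemic | 3.7 | 3.7/0.83 ≈ 4.5 | 4.2 |

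Power for 0.5 mmol/L at 32 v 31, over assumed between-woman SDs:

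| SD, mmol/L | 0.5 | 0.6 | 0.8 | 1.0 | 1.5 |
|---|---|---|---|---|---|
| Power | 97% | 90% | 68% | 50% | 26% |

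The claim therefore depends entirely on an SD that the protocol does not give. For ancestry and medication the split is given, but neither a difference nor an SD. At 36 v 27 (57:43), 90% power needs d = 0.84. The proportions alone do not show whether that is met.

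**4. Why the claim does not carry over to meal response.** Take the protocol's statement literally, as a premise: 63 women give exactly 90% for the paired meal effect. That corresponds to d = 0.415 SD of the within-woman differences. Comparing those differences between two subgroups:

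- The standard error is the overall one divided by √(p(1−p)), which is twice as large at p = 0.5.
- The expected z falls from 1.96 + 1.28 = 3.24 to 1.62, and power = Φ(1.62 − 1.96) ≈ 37%.
- The noncentral t gives 37% at 32 v 31, 36% at 36 v 27 and 33% at 42 v 21.
- For 90% at 32 v 31, the difference in response would have to be d = 0.83, twice the overall effect (0.83/0.415 = 2.0).

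**The case against.** The subgroup sentence gives its own between-group differences in glucose metrics and does not say that they are differences in meal response. Read that way, the same 63 women can have 90% power for two different comparisons. A reader might infer that the 90% is false. The documents do not support that, because 90% is attained if the SD is 0.60 mmol/L or less, and the SD may stand in the cited study. This objection stands, and it limits the power point to unsupported.

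A reader might also take 37% as the trial's real interaction power, or conclude that about 250 women are needed (4 × 63 = 252). That does not follow either. Both figures rest on 63 women giving exactly 90% for the meal effect, which the stated R² does not reproduce. With R² = 0.38 at face value, 63 women would give over 99.9% for the main effect, and an equal-sized interaction at an even split (noncentrality divided by 4) would have about 86%. An R² from an association with self-reported GI is a poor basis for a meal contrast, so 86% is no more usable than 37%.

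Not every listed covariate is a fixed trait: gestational age, physical activity and sleep quality can differ between the two occasions. This stands, but a significant main effect of such a covariate still shows neither mediation nor effect modification. Likewise, calling ancestry and medication confounders of glycaemic response is loose wording. It does not assert that they confound the within-woman comparison.

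Finally, moderation is mentioned and secondary analyses are labelled exploratory. That softens the consequence, but it does not repair an inferential rule placed in the primary-analysis paragraph, nor does it supply a basis for the 90%.

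**Conclusion.** The mediator point holds on the text alone and needs no numerical assumption. Following the plan as written would present predictors of glucose level as explanations of the protein effect.

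The power point holds in a limited form. The 90% for BMI, age and diabetes type is unsupported, since no SD and no split are given. At 32 v 31 and two-sided 0.05 it needs SDs of at most about 0.60 mmol/L, 73 (AUC) and 4.5 points. Adequate power for ancestry and medication rests on proportions alone. None of these statements can be taken to cover differences in meal response. The 37% illustrates why, under its stated premise, and is not an estimate of this trial's power.

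This should be corrected, but it does not undermine the primary comparison of the two meals.

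**What to change.** 1. In Statistical analysis considerations, replace the mediator sentence with a short, pre-named set of meal-by-covariate interactions (for example diabetes type, BMI and occasion). Report them as exploratory effect modification with confidence intervals, in line with Outcomes of interest. State that covariate main effects are adjustment terms and will not be read as explaining the meal effect.
2. In Sample size using power calculation, either delete the subgroup, ancestry and medication power claims, or restate each with its SD, its split, its target difference and the comparison it concerns. In either case, say that they do not cover differences in meal response. Do not insert 37% as the trial's power.

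The cost is a few sentences and a few model terms, with no new data and no extra recruitment. The protocol gives up a favourable power statement that it cannot at present support.
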